**Fig. 2 Fig2:**
[figure not shown]
Example of treatment content. Cases illustrating treatment procedures

### Participant safety

This study will be conducted within routine care, meaning that all patient safety procedures apply. Before the study, all patients and potential participants are assessed for suitability for online treatment (including assessment of suicide risk), patient activity (including measures) is monitored weekly, and there is a procedure for handling absence of activity, including secure messages, telephone calls, and/or letters, at different timepoints. Patients will have the option of continuing contact with their recruiting clinic for any additional treatment needs.

### Ethical considerations

All participants will provide digital informed consent in the first pre-program module of the online program. Since the study is carried out within a clinical context with treatment-seeking patients, those patients who do not wish to provide consent for research participation will nonetheless receive exactly the same treatment, but not included in study-related data collection and analysis. This study is approved by the Regional Ethics Board of Stockholm, Sweden (ref. no. 2017/1479-31), pending a minor amendment.

## Planned statistical analyses

### Acceptability measures

Descriptive statistics on treatment credibility, treatment satisfaction, and working alliance will be presented in means and standard deviations. Occurrence of possible negative effects due to psychological treatment will be presented descriptively and in frequencies, means, and standard deviations.

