**Method:**

We developed a novel Internet-delivered cognitive behavioral treatment for gambling, based on qualitative interviews with treatment-seeking gamblers, behavioral research on gambling behavior, and the pathway model for problem gambling. This research protocol describes a non-randomized pilot and feasibility trial conducted in routine addiction care with adult treatment-seeking patients (max *N* = 25) with problem gambling. The primary aim is to ensure acceptability and safety, measured by satisfaction, credibility, working alliance, and possible negative effects. Secondary aims are feasibility of study procedures in terms of recruitment and measurement procedures as well as potential effectiveness measured weekly by gambling symptoms as primary outcome and gambling behavior, quality of life, symptoms of depression and anxiety, alcohol, and drug use as secondary outcomes. Potential mediators measured weekly are loss of control, verbal rules, and well-being.

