### Objectives

The primary aim of this non-randomized pilot and feasibility trial is to ensure that a novel iCBT treatment is acceptable and safe for patients in routine care. Specifically, we aim to evaluate acceptability and safety in terms of the following:
Treatment satisfactionPossible negative effects due to psychological treatmentTreatment credibilityWorking alliance

Secondly, we aim to evaluate feasibility of the following study procedures for a future randomized controlled trial:
Recruitment procedures and recruitment ratesMeasurement procedures within the newly developed *Stöd och Behandling* (support and treatment) (SaT) platform

Thirdly, we aim to evaluate potential effectiveness and possible mediators of treatment:
Gambling symptoms as the primary outcomeGambling behavior, quality of life, symptoms of depression and anxiety, alcohol, and drug use as secondary outcomesUse of stimulus control strategies, loss of control in gambling situations, problematic gambling-related thinking, and well-being, all as possible mediators of treatment effects

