### Measures

Self-rated measures will be collected using the SaT platform from inclusion to treatment termination and using a separate online research platform for the follow-up (due to clinical policy not permitting access to the SaT platform after concluded treatment). All self-report measures apart from initial screening will be completed by the participants online on their own. See Table 1 for full list of measures and the measurement points.

**Table 1 Tab1:** Measures and measurement points

Measure	Assessment		Treatment				
	Screening	Diagnostic	Pre	Weekly	Additional	Post	Month 3
The Problem Gambling Severity Index (PGSI)	X						
The Structured Clinical Interview for Gambling Disorder (SCI-GD)		X^a^					
The Mini International Neuropsychiatric Interview version 7 (MINI-7)		X					
Consent			X^a^				
Demography			X^a^				
The Patient Health Questionnaire (PHQ-9)			X^a^			X	X
The Generalized Anxiety Disorder 7-item scale (GAD-7)			X^a^			X	X
The Alcohol Use Identification Test (AUDIT)			X^a^			X	X
The Drug Use Identification Test (DUDIT)			X^a^			X	X
The Gamblers Pathways Questionnaire (GPQ)			X^a^				
The World Health Organization Quality of Life 26 item version (WHOQOL-BREF)			X^a^			X	X
The Gambling Symptom Assessment Scale (G-SAS)			X^b^	X^b^		X	X
The Gambling TimeLine Follow Back (TLFB-G)				X^b^		X	X
Process measures^c^				X			
The Credibility/Expectancy questionnaire (CEQ)					X^d^		
The Working Alliance Inventory-Revised Short Version (WAI-SR)					X^e^		
The Client Satisfaction Questionnaire (CSQ)						X	X
The Negative Effects Questionnaire 20 items version (NEQ-20)						X	

^a^Measure is also part of a parallel psychometric study [27]

^b^Scored in reference to the week prior to seeking treatment

^c^ Process measures (possible mediators) adapted from item 15 in the Scale of Gambling Choices, item 6, 7, 8, and 13 in the Gambler’s Beliefs Questionnaire as well as well-being

^d^Administered at treatment module 2

^e^Administered at treatment module 3

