#### Acceptability and safety measures

Satisfaction with treatment and potential negative effects due to treatment will be measured with the Client Satisfaction Questionnaire—8-item version [31] and the Negative Effects Questionnaire—20-item version [32], respectively, both administered at post-treatment. Perceived credibility and expectancy will be measured with the Credibility/Expectancy questionnaire [33], administered at the end of the second introductory treatment module. Working alliance will be measured with the Working Alliance Inventory-Revised Short Version [34], at the end of the third treatment module.

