### Potential effectiveness

Scores from the Gambling Symptom Assessment Scale and TLFB-derived measures, collected weekly, will be modeled using appropriate mixed effects models [46] depending on distribution (e.g., Gaussian, lognormal, Poisson, zero-inflated versions), with maximum likelihood estimation of missing data and appropriate numeric time-variable(s) [47]. Outcome measures collected less frequently will be modeled using Generalized Estimating Equations. The results will be used to calculate power and sample size in a planned future randomized controlled trial. In the current study, we aim to recruit *n* = 25 participants to assess feasibility; assuming that sample baseline means and standard deviations on the Gambling Symptom Assessment Scale are similar to an ongoing treatment study at the same treatment center (*M* = 24.9, SD = 11), the pilot study should be able to detect a within-group effect size of at least *d* > 0.6 under realistic circumstances. See Fig. 3 for a power spectrum plot, showing what corresponding effect size (as a function of a range of post-treatment means and standard deviations) can be detected with 80% power, with different assumed within-subject correlations.

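### Safety is part of the primary aim, but the only harm result planned is the self-attributed NEQ-20 at post-treatment; individual worsening on scores already collected is not reported as a safety result

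*Protocol article*

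**What the plan says.** Under Objectives, the primary aim "is to ensure that a novel iCBT treatment is acceptable and safe for patients in routine care". The abstract names four measures for it: "The primary aim is to ensure acceptability and safety, measured by satisfaction, credibility, working alliance, and possible negative effects". Only the last of the four concerns harm.

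Under Acceptability and safety measures, satisfaction is assigned to the Client Satisfaction Questionnaire and negative effects to the NEQ-20, "both administered at post-treatment". Table 1 repeats the satisfaction questionnaire at month 3 but marks the NEQ-20 at post-treatment only. Table 2 places collection of post-measures in module 10, the last module. On mode of collection, the Measures section says: "All self-report measures apart from initial screening will be completed by the participants online on their own".

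The planned analysis, under Acceptability measures, is: "Occurrence of possible negative effects due to psychological treatment will be presented descriptively and in frequencies, means, and standard deviations". No interval is mentioned.

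The other scores that could show harm appear under Potential effectiveness: "Scores from the Gambling Symptom Assessment Scale and TLFB-derived measures, collected weekly, will be modeled using appropriate mixed effects models". Less frequent measures, among them the PHQ-9 (pre, post and month 3), go into Generalized Estimating Equations. Nowhere does the article define deterioration or plan a count of patients who worsen.

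**The concern.** Two features of the single harm measure limit what it can show. The patient must attribute the harm to treatment before it counts. It is also collected once, at the end of a ten-module programme for which 16 weeks are allowed. Those who stop early, possibly because they are doing badly, are the patients least likely to answer it.

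The weekly G-SAS has neither limitation: it needs no attribution, and it leaves a record up to the point of leaving. The plan uses it only to estimate effectiveness, where the average can improve while some individuals worsen. This pilot is meant to guide a randomised trial of content that the Discussion says has had no prior face-to-face evaluation. A safety statement resting mainly on those who finish would be a weak basis for that step.

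**Working it through.** **Inputs from the article.** n = 25; assumed G-SAS baseline SD 11; detectable within-group d of 0.6; 80% power (Potential effectiveness). G-SAS internal consistency 0.87 and test-retest reliability 0.56 (Primary outcome measure of potential effectiveness). Assumed here because the article does not state them: two-sided 5% alpha, normal change scores, equal SDs, and a within-subject correlation r of 0.5 (range 0.3 to 0.7).

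**1. The article's own figure.** For a paired t-test with n = 25, 80% power needs a standardised mean change of 0.584. On the raw-SD scale, d = 0.584 × √(2(1 − r)): 0.69 at r = 0.3, 0.58 at r = 0.5 and 0.45 at r = 0.7. The stated 0.6 is reproduced for r of about 0.5. It is not in dispute.

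**2. What an average improvement can hide.** Mean improvement = 0.6 × 11 = 6.6 points. SD of change = 11 × √(2(1 − r)) = 11.0 at r = 0.5. The share scoring worse than baseline is Φ(−6.6/11.0) = 27%, or about 7 of 25. The range is 31% (r = 0.3) to 22% (r = 0.7). These shares include measurement error and are illustrative.

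**3. Thresholds for reliable worsening.** Threshold = 1.96 × SD × √(2(1 − reliability)).
- Internal consistency 0.87: 1.96 × 11 × √0.26 = 11.0 points.
- Test-retest 0.56: 1.96 × 11 × √0.88 = 20.2 points.

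Under the assumptions of step 2, worsening beyond 11.0 points has probability Φ(−(6.6 + 11.0)/11.0) = 5.5% (range 8.8% to 2.0%). Beyond 20.2 points it is 0.7%. The choice of reliability matters, so both should be shown.

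**4. Which score to count.** Suppose no true change, SD 11, independent normal error and 12 post-baseline assessments (an assumed number). The table gives the share of patients flagged by a rise beyond 11.0 points.

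| True reliability | Last score only | Any of 12 visits |
|---|---|---|
| 0.87 | 2.5% | 16% |
| 0.56 | 14% | 54% |

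With 5 to 16 assessments, the any-visit share is 9% to 19% at reliability 0.87 and 38% to 59% at 0.56. At 12 assessments, that is 4 to 13 of 25 patients flagged by noise alone. Under 0.56, the 20.2-point threshold brings the last-score rate back to 2.5%.

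**5. What 25 patients can exclude.** With zero events, the exact two-sided 95% upper limit is 1 − 0.025^(1/25) = 13.7%. With 3 events in 25, the exact interval is 2.5% to 31.2%. If only 15 answered the NEQ-20 (an assumed number, for illustration), zero events gives 1 − 0.025^(1/15) = 21.8%.

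**The case against.** The strongest defence is that this is a small uncontrolled pilot, for which descriptive reporting of a named negative-effects questionnaire is coherent, and that intervals and reliable-change definitions are usual content for an analysis plan. The second part has force for the details. It does not remove the point, because the article itself fixes which measure carries safety, when it is given and how it is summarised. The remedy is also descriptive.

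Several stronger readings are tempting, but the article does not support them.

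- **That patients are unprotected.** Platform and Participant safety describe suicide-risk assessment beforehand, weekly monitoring that includes the measures, and telephone calls for inactivity or signs of suicidality. These provisions are real; what is missing is a reported outcome drawn from them.
- **That the trial will certify safety.** The verb 'ensure' in the aim suggests this, but Objectives goes on to say that acceptability and safety will be evaluated, the Discussion says the same, and no rule for declaring safety is planned.
- **That the sample size rests only on a G-SAS effect.** The article gives feasibility as the purpose of the 25 participants; the detectable effect follows as support.
- **That symptom scores are used only as mean curves.** Mixed models carry subject-level effects, and the mediator analysis correlates individual changes. Neither is planned as a safety result.
- **That any 11-point rise at any visit should count as harm.** Step 4 of the working shows how many false signals this would give.

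It also stands that, without a control arm, deterioration cannot be attributed to treatment. The article says as much of its observed effects.

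**Conclusion.** The point holds in a limited form. The reported safety result depends on one self-attributed questionnaire given at post-treatment, and individual worsening on scores already collected is not part of it. Following the plan as written would base the safety result mainly on those who finish. How many patients would be missing cannot be computed, because the article gives no expected dropout and does not say whether early leavers are still asked for post-measures.

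The size that can be stated is the precision: with all 25 observed and no events, true rates up to 13.7% remain compatible with the data. The 27% and 5.5% shares rest on normal change scores, d = 0.6 and r = 0.5. They show only that average improvement and individual worsening can coexist; they do not predict a harm rate. This is a worthwhile and cheap improvement to the stated analysis, not a flaw that invalidates the trial.

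**What to change.** In Planned statistical analyses, under Acceptability measures, add a descriptive safety table with these entries.

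1. **G-SAS.** Among all participants with any post-baseline G-SAS, the number and percentage, with exact 95% confidence interval, whose last available score exceeds baseline by the reliable-change threshold. Early leavers contribute their last weekly score. Prespecify the threshold and show both 11.0 points (internal consistency 0.87) and 20.2 points (test-retest 0.56). Do not count a rise at any single visit.
2. **PHQ-9.** Worsening from pre to post or month 3, reported in the same way, with a prespecified threshold; the article gives no figures from which to derive one.
3. **TLFB-G loss.** Include it only once its baseline is defined. Table 1 has no Pre mark for it, and a footnote refers its weekly entry to the week before treatment was sought.
4. **NEQ-20.** Frequencies with exact 95% confidence intervals, and the number of respondents out of all who started.

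State that the trial estimates safety, and that zero events in 25 excludes only true rates above 13.7% (two-sided 95%).

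The cost is one extra table from scores already scheduled, plus the definitions above. The safety statement will be less reassuring, and the rates, being uncontrolled, cannot be read as caused by treatment.

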### Potential effectiveness

Scores from the Gambling Symptom Assessment Scale and TLFB-derived measures, collected weekly, will be modeled using appropriate mixed effects models [46] depending on distribution (e.g., Gaussian, lognormal, Poisson, zero-inflated versions), with maximum likelihood estimation of missing data and appropriate numeric time-variable(s) [47]. Outcome measures collected less frequently will be modeled using Generalized Estimating Equations. The results will be used to calculate power and sample size in a planned future randomized controlled trial. In the current study, we aim to recruit *n* = 25 participants to assess feasibility; assuming that sample baseline means and standard deviations on the Gambling Symptom Assessment Scale are similar to an ongoing treatment study at the same treatment center (*M* = 24.9, SD = 11), the pilot study should be able to detect a within-group effect size of at least *d* > 0.6 under realistic circumstances. See Fig. 3 for a power spectrum plot, showing what corresponding effect size (as a function of a range of post-treatment means and standard deviations) can be detected with 80% power, with different assumed within-subject correlations.

**Fig. 3 Fig3:**
[figure not shown]
Power curves as a function of post-treatment means, SDs, and within-r, with line weights according to resulting effect size

We will explore possible mediators of treatment effects by examining correlations between change in symptoms and change in the process measures, and we will also explore time-lagged effects. Descriptive statistics on acceptability measures and platform activity (completed modules, number of logins, etc.) will also be presented.

## Discussion

This non-randomized trial aims to evaluate the acceptability, feasibility, potential effectiveness, and possible negative effects of a novel iCBT protocol in a sample of treatment-seeking participants with problem gambling within routine care. The study is innovative in several respects.

Firstly, the study will be conducted in routine care for problem gambling with a sample of treatment-seeking patients, most of whom are expected to meet criteria for gambling disorder. The external validity of the study will thus be very high. All treatment-seeking patients, including those with comorbidities, will be offered iCBT. This is uncommon, as patients with comorbidities are often excluded from treatment studies as well as from gambling treatment within routine care. A further advantage with iCBT is that it can reduce the waiting time to initiate treatment. The waiting time for group treatment for problem gambling at the Stockholm Center for Dependency Disorders can vary greatly between clinics and seasons: patients may have to wait between 1 and 12 months, depending on demand; such a long wait is often too long when considering treatment-relevant factors such as motivational windows that often co-occur with treatment-seeking [48].

Second, we have used a bottom-up approach in the treatment development process. This includes deriving the treatment content from in-depth clinical interviews with treatment-seeking gamblers, research on the learning, and maintenance processes of gambling behavior, as well as the pathway model for PG [2]. Also, we designed the treatment protocol to build on a simple, delimited set of interventions of presumed greatest importance. This is contrary to typical addiction treatments that offer a smorgasbord of exercises and treatment rationales in an attempt to capture all relevant aspects that may apply differently to different patients. As a research field, the study of treatment for problem gambling is still in its infancy. Current CBT protocols for problem gambling are seldom based on a functional analysis on why problem gambling behavior persists over time despite negative consequences. This is so, despite the fact that problem gambling is a phenomenon that has generated basic research on the learning processes involved. In general, a broad mixture of general CBT components, which have been found effective for other conditions such as depression, anxiety, or alcohol problems, have often been arbitrarily combined into treatment protocols [49], while interventions targeting key gambling processes such as “chasing losses,” or “loss of control” [2, 50] have been lacking. In contrast, utilizing a few, carefully selected treatment components, will hopefully enable a more clear definition of what to prioritize in treatment, opportunities for continuous applied behavior change, as well as better controlled studies in terms of mediating and moderating factors.

Third, this study aims to evaluate novel treatment content in an iCBT format without prior face-to-face evaluation. This is uncommon, but in view of the large body of evidence indicating that iCBT yields outcomes comparable to face-to-face treatment [51], the increasing acceptance of iCBT as a treatment form, and the availability of an eClinic within the Stockholm Center for Dependency Disorders as the trial setting, we have opted to eliminate the step of face-to-face evaluation, instead using telephone and video meetings, prior to the iCBT launch in this pilot and feasibility trial. Additionally, we see the use of the nationally available SaT digital platform, as enabling rapid development, deployment and dissemination, evaluation, and optimization of novel treatment interventions into routine care.

The study will also be subject to some limitations. A non-randomized pilot and feasibility trial will not yield knowledge on whether observed effects are causal, nor enable evaluation of effects for specific subgroups of gamblers through randomization to typical or subgroup-tailored treatment. By design, this single-arm study will only provide an uncontrolled estimate of the treatment effect and not of the spontaneous remission or treatment-as-usual, to which the treatment effect will be compared in future randomized trials. However, non-randomized pilot trial designs are common as a first step in the development and evaluation of novel interventions. Apart from evaluating acceptability, feasibility, possible effectiveness, and potential negative effects, the pilot outcomes of this study will hopefully provide some clues as to whether further treatment adaptations for problem gambling and comorbidity specifically, might be necessary, a research question which can then be explored in a future randomized controlled trial.

## Data Availability

No data is available.

## Abbreviations

CBT: Cognitive behavioral therapy
DSM-5: Diagnostic and Statistical Manual of Mental Disorders, 5th edition
iCBT: Internet-delivered cognitive behavioral therapy
ISRII: International Society for Research on Internet Interventions
REGAPS: Responding to and Reducing Gambling Problems–Studies in Help-seeking, Measurement, Comorbidity and Policy Impacts
SaT: The *Stöd och Behandling* (support and treatment) platform
